# 1. Objectives of the study

### 1.1 Primary objective

The primary objective is to assess the impact of osteopathic treatment on back-chest pain in adult patients with cystic fibrosis.

### 1.2 Secondary objectives

The secondary objectives are to assess the impact of osteopathic treatment:
• neck pain
• headache
• quality of life.

## 2. Trial Design

MUCOSTEO is a randomized controlled multicenter study with three parallel arms of a total duration of 24 months (duration of participation: 6 months).

Eligible patients for this study are patients with cystic fibrosis and with chest, neck and / or back pain. After obtaining consent, patients will be randomized into 3 groups: a group receiving a general osteopathic treatment, a group receiving a specific osteopathic treatment (sham treatment) and an untreated group.

The treatment allocation will be done through a centralized randomization at URC (Clinical trial Unit), from a list of block randomization. Patient and physician investigator will be unaware of the allocation of patients in groups 1 and 2. Only the osteopathic practitioner will know the result of randomization.

After the initial visit during which randomization occurs, patients randomized in groups 1 and 2 will be monitored every month until M6 by the osteopathic practitioner. Patients in all three groups will be reviewed at M3 and M6 to collect evaluation criteria including assessment of pain, quality of life questionnaires and osteopathic assessment.

|  | **M0** | **M1** | **M2** | **M3** | **M4** | **M5** | **M6** |
| --- | --- | --- | --- | --- | --- | --- | --- |
| Inclusion /signature of consent | X |  |  |  |  |  |  |
| Randomization | X |  |  |  |  |  |  |
| Evaluation of pain | X |  |  | X |  |  | X |
| Quality of life questionnaire | X |  |  | X |  |  | X |
| Clinical exam | X |  |  | X |  |  | X |
| PFT (FEV1) | X |  |  | X |  |  | X |
| concomitant therapies (including analgesics) | X |  |  | X |  |  | X |
| Osteopathic evaluation | X |  |  | X |  |  | X |
| General (group 1) or specific (group 2) osteopathic treatment | X | X | X | X | X | X |  |
| Adverse events |  | X | X | X | X | X | X |

## 3. Study Population

**Inclusion criteria:**

- Diagnosis of cystic fibrosis (positive sweat test and/or two CFTR disease-causing mutations)
- Age older than 18
- Patient with chest, neck or back pain (VAS> 2 or use of analgesics in the month before enrollment)
- Signature of consent
- Health insurance

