# 6. Statistical analysis plan

## 6.1. Definition of endpoints

### 6.1.1 Primary endpoint

For the primary analysis, a composite endpoint will be used. For each patient the following two parameters will be averaged:

1) The evaluation of chest and back pain on the previous month (VAS 0 to 10)

2) (The number of days in the month when the patient experienced chest back pain / Total days of the previous month) *10 (score from 0 to 10)

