### 6.1.2 Secondary endpoints

Secondary endpoints are:

- The mean between (the evaluation of neck and trapezus pain on the previous month) and (the number of days in the month when the patient experienced neck and trapezus pain) / (total days of the previous month) *10.
- The mean between (the evaluation of headache on the previous month) and (the number of days in the month when the patient experienced headache) / (total days of the previous month) *10.
- For quality of life, each of the 4 studied scores (physical functioning, energy / well-being, body image and respiratory symptoms) will be standardized (values ranging from 0 to 100). The average of these four standardized scores will be used as an endpoint.

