## 6.3. Statistical analysis

### 6.3.1 Population analysis

Only the intent-to-treat (ITT) population will be analyzed. The ITT population was defined as all randomized subjects. They will be analyzed in the group they were randomized regardless of the treatment actually received, regardless of their fate in the study.

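### Neck pain alone qualifies a patient for a trial whose primary endpoint is chest and back pain, which dilutes the effect behind the stated 80% power

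*Combined protocol and SAP*

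**What the plan says.** **Entry.** Section 2 describes the eligible population as "patients with cystic fibrosis and with chest, neck and / or back pain". Section 3 repeats this as "Patient with chest, neck or back pain (VAS> 2 or use of analgesics in the month before enrollment"). Any one of the three sites is enough.

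**Question.** Section 1.1 states: "The primary objective is to assess the impact of osteopathic treatment on back-chest pain in adult patients with cystic fibrosis". Neck pain appears only among the secondary objectives (section 1.2).

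**Endpoint.** Section 6.1.1 averages two parts, each scored 0 to 10: "The evaluation of chest and back pain on the previous month (VAS 0 to 10") and "The number of days in the month when the patient experienced chest back pain / Total days of the previous month", the latter multiplied by 10. Neck and trapezius pain has its own composite in section 6.1.2, using "the number of days in the month when the patient experienced neck and trapezus pain".

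**Population and model.** Section 6.3.1: "The ITT population was defined as all randomized subjects". Section 6.3.3 compares the M6 composite with a random-intercept mixed model. It names no baseline or pain-site term. Section 2 describes block randomisation and names no stratification factor. No section sets a minimum chest/back score at M0.

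**The concern.** The plan treats neck pain as a different outcome from chest/back pain, yet accepts it as the only qualifying symptom for a trial of chest/back pain. The primary composite cannot go below 0. A patient who enters with neck pain and no chest/back pain is already at that floor, so a treatment that relieves chest/back pain has nothing to relieve in that patient.

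Each such patient contributes no benefit to the average difference. If the analysis does not account for the M0 score, these patients also widen the spread of M6 values, because low scorers are mixed with patients in the middle of the scale. With 16 patients on each side of the primary comparison and power planned at 80%, there is little margin for either effect. Without stratification by pain site, chance could also place more floor patients on one side than on the other.

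**Working it through.** **Inputs from the documents.** Group 1 has 16 patients; groups 2 and 3 pooled have 8 + 8 = 16. The planned difference is about 1 SD, with a two-sided 5% test and 80% power (sections 6.2 and 6.3.3).

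**Step 1: reproduce the plan's figure.** The noncentrality is d / √(1/16 + 1/16) = 2.828 × d, where d is the difference in SD units.
- Normal approximation at d = 1: Φ(2.828 − 1.960) = Φ(0.868) = 80.7%.
- Noncentral t with 30 degrees of freedom: 78.1%.

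The stated 80% reproduces, so the sample-size arithmetic is not at fault.

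**Step 2: dilution with the SD held fixed.** Let f be the share of randomised patients with no chest/back pain at M0. The documents do not give f, so 10%, 20% and 30% are assumptions. Of 32 patients these are 3.2, 6.4 and 9.6. Assume also that these patients have no treatment effect and the others have 1 SD. The average effect is then (1 − f) SD.

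| f | Average effect | Power, t | Power, normal | Total N for 80% (normal) |
|---|---|---|---|---|
| 0% | 1.0 SD | 78% | 81% | 32 |
| 10% | 0.9 SD | 69% | 72% | 40 |
| 20% | 0.8 SD | 59% | 62% | 50 |
| 30% | 0.7 SD | 48% | 51% | 66 |

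**Step 3: let the SD change, with no use of M0.** Assume a control mean 2 SD above zero and floor patients at 0. At f = 20%:
- control variance = 0.8 + 0.2 × 0.8 × 2² = 1.44
- treated variance = 0.8 + 0.2 × 0.8 × 1² = 0.96
- pooled SD = √1.20 = 1.10
- normal-approximation power = 54%

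A simulated t-test on M6 scores (control mean 4, SD 2, effect 2, scores limited to 0–10, floor patients near 0) gives about 63%, 50% and 39% at f = 10%, 20% and 30%, against 78% at f = 0.

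**Step 4: use M0.** The same scenario with the M0 score as a covariate, at an assumed M0–M6 correlation of 0.5, gives about 86% at f = 0, then 82%, 76% and 68%. Repeated simulation runs differ by about a point. With correlation 0.3 the series is about 79%, 72%, 65%, 56%; with 0.7 it is about 96%, 94%, 89%, 84%.

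**Step 5: would dropping floor patients do better?** With M0 adjustment and correlation 0.5, restricting to patients with chest/back pain at M0 gives about 82%, 77% and 70%, against 82%, 76% and 68% when everyone is kept. The gain is negligible.

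**The case against.** The best defence has four parts.

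**The number of floor patients may be small or zero.** The criteria permit them; nothing shows that they will enter, and a patient who qualifies on neck pain may also have chest or back pain. This stands. The power losses are conditional on an assumed share.

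**The planned model may already absorb part of the loss.** Section 6.3.3 specifies a repeated-measures mixed model, and pain is recorded at M0, M3 and M6, so an M6-only comparison may be too pessimistic. This stands in part. The section does not say how M0 enters the model, so the protection cannot be assumed. Even with adjustment, power still falls by 10 points at f = 20% (86% to 76%).

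**The 1 SD may already describe the mixed population.** Section 6.2 does not say that it refers only to patients with chest/back pain. This is fair, and it is why that premise is labelled an assumption. But section 6.2 does not mention patients without the target symptom either.

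**This is a pilot in a rare disease, where broad entry helps recruitment.** That is a reason to offer an alternative to narrower entry. It does not remove the mismatch, because the same section claims 80% power.

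A reader might also infer that the analgesic route creates a second floor, since a patient can enter with a VAS of 2 or less. The documents do not support that. Half of the composite is pain days, so a patient with chest/back VAS 2 and pain every day scores (2 + 10) / 2 = 6 and has ample room to improve. The analgesic use can also be read as relating to the listed pain, which leaves only the question of site.

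**Conclusion.** The mismatch is explicit in the text: entry on neck pain alone, a primary endpoint confined to chest/back pain, and all randomised patients analysed. A patient with no chest/back pain at M0 can show only no change or worsening.

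The consequence is loss of power. It would go too far to infer bias: random allocation keeps the comparison unbiased in expectation, and floor patients can still worsen, so they are not wholly uninformative. Nor is the sample-size calculation wrong on its own terms.

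The size depends on three things the documents do not give: the share of such patients, whether the 1 SD applies only to the others, and how M0 is used. At an assumed 20%, power is between about 50% (M0 ignored) and 76% (M0 adjusted, correlation 0.5); the matching values with no such patients are 78% and 86%. This should be fixed. It is an efficiency problem of unknown size with an inexpensive remedy, so it does not rank as a fatal defect.

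**What to change.** **Preferred.** Amend the pain criterion in section 3, and the matching sentence in section 2, so that the qualifying pain is chest or back pain at M0. Neck pain and headache stay as secondary outcomes. Cost: a one-line eligibility amendment and somewhat slower recruitment; the documents give no figure from which to size the delay.

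**If broad entry is kept.** Leave all randomised patients as the primary analysis set. In section 6.3.3, add the M0 chest/back composite, already collected from every patient at enrollment (section 4), as a covariate in the primary model. Pre-specify a supportive analysis in patients with chest or back pain at M0. Cost: one model term and one extra analysis, with no effect on recruitment. Replacing the all-randomised set with that subset as the primary analysis is not recommended: once M0 is in the model it adds almost no power, and it departs from section 6.3.1.

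Under this second option, section 6.2 should also state the share of patients without chest/back pain that the 80% power allows for.

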**Non inclusion criteria :**

- Regular treatment of the patient by an osteopathic practitioner in the previous 3 months
- Patient on a lung transplant waiting list
- History of lung transplantation
- Pregnant woman
- Difficulties in understanding not allowing care
- Patient participation in another therapeutic clinical trial protocol

##

## 4. Data collection

**At enrollment:**

*For all patients*

- Patient's identification (first letter of first name and first letter of name)
- Sex
- Date of signature of consent
- Age at enrollment
- Randomization arm
- Verification of inclusion and non inclusion criteria
- Collecting medical history
- Clinical exam
  - Date of exam
  - Age
  - Height
  - Weight
  - Pulmonary Function tests (FVC, FEV1)
  - Pulmonary infections
  - Clinical observation (Respiratory tract, digestive tract, cardio-vascular system, neurological system, skin condition, general condition)
- Assessment of pain (mean VAS and number of days in the previous month):) for :
  - neck and trapezus pain
  - chest and back pain
  - Headache
- Other pain (location, VAS, start date, end date, medication)
- Taking analgesics, NSAIDs, muscle relaxants or antidepressants during the previous month (name, dose, route, start date, end date, note)
- Osteopathic assessment (assessed area, severity, major or specific somatic dysfunction)
- Self-administered questionnaire of quality of life, specific for cystic fibrosis
  - physical functioning
  - energy/well-being
  - body image
  - respiratory symptoms

**Visits at M1 and M2**

*For patients in groups 1 and 2 (groups with osteopathic treatment)*

- Date of visit
- Monitoring patient notebook
- Reporting adverse events
- Painful episodes over the last month (location, VAS, start date, end date , medication)
- Taking analgesics, NSAIDs , muscle relaxants or antidepressants over the last month (dosage, route , start date, end date , indication)

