**Visit at M3**

*For all patients*

- Clinical examination
  - Date of examination
  - Age
  - Height
  - weight
  - Pulmonary function test (FVC, FEV1)
  - Pulmonary infections
  - clinical examination (respiratory, digestive, cardiovascular, neurological, skin condition , general condition)
- Assessment of pain (mean VAS and number of days in the previous month) for :
  - Neck and trapezes pain
  - Chest and back pain
  - Headache
- Other pain (location, VAS, start date, end date, medication)
- Taking analgesics, NSAIDs , muscle relaxants or antidepressants over the last month (dosage, route , start date, end date , indication)
- Osteopathic results (assessed area, severity, major or specific somatic dysfunction)
- Self-administered questionnaire of quality of life, specific for cystic fibrosis
  - physical functioning
  - energy/well-being
  - body image
  - respiratory symptoms

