**Visits at M4 and M5**

*For patients in groups 1 and 2 (groups with osteopathic treatment)*

Same data as for visits 1 and 2

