**Visit at M6**

*For all patients*

- Same data as for visit 3
- Satisfaction questionnaire

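### Section 4 contradicts the schedule on adverse events: it omits them from the all-patient M3 and M6 lists and prompts for them only in the two treated groups

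*Combined protocol and SAP*

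**What the plan says.** Section 2 (Trial Design) and Section 4 (Data collection) each set out what is recorded at which visit.

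- **Schedule table, Section 2.** The adverse-event row reads "Adverse events | | X | X | X | X | X | X": blank at M0, marked at M1 to M6. It carries no group label, whereas the osteopathic treatment row directly above it names groups 1 and 2.
- **Who attends, Section 2.** "patients randomized in groups 1 and 2 will be monitored every month until M6 by the osteopathic practitioner". For the untreated group, the visits after M0 are the common ones: "Patients in all three groups will be reviewed at M3 and M6 to collect evaluation criteria".
- **Section 4, M1 and M2.** The list is headed "For patients in groups 1 and 2 (groups with osteopathic treatment" and includes "Reporting adverse events".
- **Section 4, M4 and M5.** For the same two groups: "Same data as for visits 1 and 2".
- **Section 4, M3, all patients.** The list covers examination, lung function, pain, medication ("Taking analgesics, NSAIDs , muscle relaxants or antidepressants over the last month (dosage, route , start date, end date , indication"), osteopathic results and quality of life. It has no adverse-event item.
- **Section 4, M6, all patients.** "Same data as for visit 3", plus a satisfaction questionnaire, so again no adverse-event item.

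Section 5 adds a general rule: any adverse event that is observed goes into a dedicated part of the CRF, and any serious adverse event is notified to the sponsor. Neither duty is limited by group or visit. Section 6 describes no adverse-event endpoint or analysis.

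**The concern.** The two descriptions of data collection cannot both be followed. They differ at M3 and M6, the only follow-up visits that all three groups attend. A site or data manager working from the Section 4 lists would ask treated patients about adverse events four times and untreated patients not at all.

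Two things are at stake. The first is completeness of safety data. The schedule places treatment sessions at M0 to M5, and the last adverse-event item in Section 4 is at M5. What happens after the M5 session therefore has no listed place to be recorded. The second is fairness of any comparison with the untreated group. If one arm is asked more often than another, it will tend to report more minor events even when the true rates are equal. The untreated group is the arm that would show the background rate of events in adults with cystic fibrosis, so poor ascertainment there matters for interpretation.

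**Working it through.** The plan gives no figure of its own on this point, so there is none to reproduce. The check is a count of planned adverse-event collection points under each text.

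**Inputs.** Group sizes are from Section 6.2: group 1 = 16, group 2 = 8, group 3 = 8, total 32. Attendance is from Section 2: groups 1 and 2 monthly to M6, group 3 at M3 and M6. Adverse-event items are from the Section 2 table and the Section 4 lists.

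**Step 1. The texts side by side.**

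| Visit | Groups attending | Schedule (Section 2) | Section 4 list |
| --- | --- | --- | --- |
| M1 | 1, 2 | marked | listed |
| M2 | 1, 2 | marked | listed |
| M3 | 1, 2, 3 | marked | not listed |
| M4 | 1, 2 | marked | listed, by reference to M1 and M2 |
| M5 | 1, 2 | marked | listed, by reference to M1 and M2 |
| M6 | 1, 2, 3 | marked | not listed, by reference to M3 |

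**Step 2. Collection points per patient** (visits that the group attends and at which the item appears).

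- Section 4: groups 1 and 2 have M1, M2, M4, M5 = 4. Group 3 has 0.
- Schedule: groups 1 and 2 have M1 to M6 = 6. Group 3 has M3, M6 = 2.

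**Step 3. Patient-visits** (group size × collection points).

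| Source | Group 1 | Group 2 | Group 3 | Total |
| --- | --- | --- | --- | --- |
| Section 4 | 16 × 4 = 64 | 8 × 4 = 32 | 8 × 0 = 0 | 96 |
| Schedule | 16 × 6 = 96 | 8 × 6 = 48 | 8 × 2 = 16 | 160 |

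The difference is 160 − 96 = 64 patient-visits. This is 32 patients × 2 visits, that is, all of M3 and M6. It is 64/160 = 40% of the scheduled collection points.

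**Step 4. What remains after reconciliation.** If the schedule governs, treated patients still have 6/2 = 3 times as many collection points as untreated patients, at one-month rather than three-month spacing. Adding the missing items therefore resolves the contradiction but not the imbalance. The imbalance has to be dealt with in how any comparison is made.

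**Step 5. General versus sham.** Groups 1 and 2 have the same number and timing of collection points under either text (4 and 4, or 6 and 6).

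**The case against.** The strongest reply is that the plan, read as a whole, does provide for adverse events in group 3. The schedule marks them at M3 and M6 without a group limit, and the authors labelled the treatment row where they meant a restriction. Section 5 requires observed events and serious adverse events to be recorded in every arm. The all-patient visits include an examination by body system, lung function and pulmonary infections, so events can come to light. Section 4 and the table are not exact mirrors anyway: the M6 satisfaction questionnaire is in one and not in the other. On this view the omission is a drafting slip.

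Much of that stands, and it rules out several stronger readings that a reader might infer:

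- *Untreated patients have no planned adverse-event collection.* Not supported. That is true of the Section 4 lists alone, but the schedule and Section 5 both cover group 3.
- *The arms cannot be compared on safety.* Not supported. General and sham treatment have matching adverse-event visits. Nor does Section 6 plan a between-arm safety test that would be invalidated.
- *The primary endpoint is biased because only treated groups keep a notebook.* Not supported. Section 4 mentions a patient notebook at the monthly visits but does not describe its content or say that it informs the M3 and M6 pain answers. All groups give mean VAS and number of pain days for the same preceding month.
- *Treated arms would show a calculable multiple of the untreated event rate.* The documents give no capture rates, so any such factor would rest wholly on assumption.

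What does not stand is the idea that Section 5 cures the gap. It governs events once observed, and it sets no question, visit or recall period. Nor does a drafting slip need no repair, since CRFs are built from visit lists. It is also fair to say that monthly contact in the treated arms alone follows from having an untreated arm. That explains the imbalance but does not remove its effect on a comparison.

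**Conclusion.** The contradiction is real and should be corrected. Section 4 gives 4/4/0 collection points per patient in groups 1/2/3 and the schedule gives 6/6/2. Following Section 4 would drop M3 and M6, leave untreated patients unprompted throughout, and leave the period after the M5 session without a listed collection point in any arm. Under either text, a safety comparison with the untreated group would be subject to unequal ascertainment. The direction to expect is fewer reported events in group 3. The size cannot be derived from the documents.

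This rests on two assumptions: that the CRF follows the written visit lists, and that group 3 has no adverse-event contact beyond M3 and M6. The finding does not touch the primary pain analysis or the matching of adverse-event visits between general and sham treatment.

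**What to change.** Reconcile Section 4 with the schedule and settle how group 3 is ascertained:

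1. Add the adverse-event item to the M3 and M6 lists in Section 4 for all three groups. Use the same question in each arm, covering the interval since the last common visit (M0 to M3, then M3 to M6).
2. State in Section 6 that any adverse-event comparison with group 3 uses those two common visits only, with each event counted once.
3. Keep the monthly reports at M1, M2, M4 and M5 as additional safety data for groups 1 and 2, described separately.

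The cost is one CRF item at two existing visits and a short addition to Section 6, with no extra visit. The small downside is that treated patients are asked again about events that they have already reported, which is why the count-once rule is needed.
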